## Abstract

**Background and aims:**

Primary percutaneous coronary intervention (PPCI) is the most effective treatment strategy for ST-segment elevation myocardial infarction (STEMI). Nevertheless, dysregulated inflammation induced by myocardial reperfusion injury may increase the final infarct size and induce maladaptive myocardial remodeling. Proprotein convertase subtilisin/kexin 9 (PCSK9) inhibitor, as a novel and potent lipid-lowering drug, plays an important role in inflammation. The aim of this study is to investigate whether the early application of PCSK9 inhibitor can increase the myocardial salvage index (MSI) and improve ventricular remodeling in patients with STEMI.

**Design:**

The PERFECT II trial is a prospective, open-label, multicenter, randomized controlled study involving 160 patients with STEMI who are scheduled to undergo PPCI. The eligible patients will be divided into PCSK9 inhibitor group and control group *via* the interactive web response system, at a 1:1 ratio. In the PCSK9 inhibitor group, the PCSK9 inhibitor alirocumab at a dose of 75 mg will be subcutaneously injected immediately after PPCI and administered every 2 weeks thereafter for 3 months based on conventional treatment. In the control group, conventional treatment will be administered. The primary endpoint is MSI, as measured by cardiac magnetic resonance imaging (CMR) at 1 week after PPCI. The secondary endpoints are the peak time of creatine kinase (CK)-MB and troponin I (TnI)/TnT after PPCI; the postoperative fall time of the ST segment on electrocardiography (ECG); the rate of plasma low-density lipoprotein cholesterol (LDL-C) compliance (< 1.4 mmol/L and a reduction of >50% from baseline) at 1, 3, and 6 months after PPCI; infarct size and ejection fraction (EF) measured by CMR at 6 months after PPCI; the occurrence of major adverse cardiovascular event (MACE: a composite of cardiovascular death, non-fatal myocardial infarction, stent thrombosis, repeat revascularization, stroke, and heart failure needed to be hospitalized).

**Conclusions:**

This is the first multicenter study to investigate the effect of early application of the PCSK9 inhibitor alirocumab on MSI in patients with STEMI undergoing PPCI. The findings will provide an opportunity to explore novel ideas and methods for the treatment of acute myocardial infarction.

**Trial registration:**

ClinicalTrials.gov, identifier: NCT05292404.

## Introduction

Primary percutaneous coronary intervention (PPCI) with drug-eluting stent is an effective and common treatment strategy for acute coronary syndrome (ACS), including unstable angina (UA), non-ST-segment elevation myocardial infarction (non-STEMI), and STEMI (1). Over the past decade, the prognosis of acute myocardial infarction (AMI) has improved substantially. However, it is still the leading cause of morbidity and mortality worldwide (2). Myocardial reperfusion is imperative to salvage the ischemic myocardium in patients with STEMI; nevertheless, early restoration of blood flow itself can induce damage to the myocardium by triggering a series of sterile inflammatory responses known as myocardial ischemia-reperfusion injury (3). Crucially, the lack of effective therapy to attenuate local inflammation after myocardial infarction in patients with STEMI makes it necessary to identify a viable target for cardioprotection.

Proprotein convertase subtilisin/kexin 9 (PCSK9), which is mainly secreted by the liver, can increase the concentration of serum low-density lipoprotein cholesterol (LDL-C) by promoting LDL receptor (LDLR) degradation (4). The plasma concentration of PCSK9 is significantly increased in patients with AMI (5). Recent evidence suggests that PCSK9 contributes to inflammation beyond cholesterol regulation. In atherosclerosis progression, PCSK9 activates proinflammatory cytokine production and affects oxidative modifications within atherosclerotic lesions (6, 7). In addition, in animal models of AMI, PCSK9 is up-regulated mostly in the region bordering the infarct area and determines the development of infarct size, cardiac function, and autophagy (8). Additionally, the concentration of serum PCSK9 is associated with the future risk of cardiovascular disease (9). PCSK9 inhibitors like alirocumab are frequently performed to reduce the concentration of LDL-C and lower the rate of adverse cardiovascular events (10). Moreover, application of alirocumab and the anti-PCSK9 AT04A vaccine in APOE^*^3Leiden.CETP transgenic mice reduces vascular inflammation and atherosclerotic lesions (11, 12). Our team found that PCSK9 knockout mice showed ameliorated myocardial inflammation and heart failure after myocardial infarction.

We recently conducted a randomized pilot study (PERFECT trial, NCT04731105) in 20 patients with anterior myocardial infarction accompanied by chest pain that began within 24 h. In this study, a single 75-mg dose of alirocumab was subcutaneously injected immediately after PPCI and lead to a trend toward an increase in the myocardial salvage index (MSI) compared with the control group (0.50 ± 0.16 vs. 0.41 ± 0.15; *p* = 0.21).

To further confirm the results of the PERFECT trial, we designed this multicenter, randomized controlled study to investigate whether early application of alirocumab in patients with STEMI can increase the MSI 1 week after injection and decrease the infarct size 6 months later. The MSI, as assessed by cardiac magnetic resonance imaging (CMR) with late gadolinium enhancement, is considered to be the gold-standard method to assess of infarct size (13). Thus, we will use the MSI, instead of infarct size, as the primary endpoint in this study.

## Methods

### Study objectives

The primary objective of this study is to explore whether the early application of the PCSK9 inhibitor alirocumab after successful PPCI increases the MSI, limits infarct size, and improves ventricular remodeling in patients with STEMI.

### Study design

The PERFECT II trial is a multicenter, prospective, open-label, randomized controlled clinical trial. The centers of this study include Tongren Hospital, Chest Hospital, Tenth People's Hospital, and Ninth People's Hospital in Shanghai. STEMI patients with an onset of within 24 h who are scheduled to undergo PPCI will be randomized in a 1:1 fashion to receive alirocumab (PCSK9 inhibitor treatment group) or conventional treatment (control group); each group will include 80 eligible patients. The study flow chart is shown in Figure 1.

**Figure 1 F1:**
[figure not shown]
Study flow chart. STEMI, ST-segment elevation myocardial infarction; PPCI, primary percutaneous coronary intervention; sc, subcutaneous; MSI, myocardial salvage index; LDL-C, low-density lipoprotein cholesterol; EF, ejection faction; MACE, major adverse cardiovascular event.

**Inclusion criteria**
1. Patients aged 18 to 80, inclusive but not 18
2. STEMI patients with an onset of within 24 h who are scheduled to undergo PPCI with drug-eluting stent
3. Patients who have provided written informed consent
**Exclusion criteria**
1. Patients who are allergic to PCSK9 inhibitors and aspirin
2. Patients with multivessel disease who are scheduled to undergo elective intervention within 6 months
3. Patients who have undergone revascularization or treatment with PCSK9 inhibitors previously
4. Women who are known to be pregnant, breastfeeding, or preparing for pregnancy in the following 6 months
5. Life expectancy of < 6 months
6. Severe hepatic or renal dysfunction (ALT >5-fold ULA, eGFR < 15 mL/min/1.73 m^**2**^)
7. Active malignant tumor
8. Patients considered to be unsuitable for participation in this study by the investigator

### Randomization

Randomization procedures will be conducted strictly before PPCI. Eligible patients will be randomized 1:1 to the PCSK9 inhibitor group or the control group and stratified by age (≤ 60/>60; 2 categories), gender (female/male; 2 categories), time from symptom onset (< 3/3–24 h; 2 categories) using the interactive web response system (IWRS) after providing written informed consents.

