### Study endpoints

The primary endpoint is MSI measured by CMR at 1 week after the index PPCI. The secondary endpoints are the peak time of CK-MB and TnI/TnT after PPCI; the postoperative fall time of the ST segment on ECG; the rate of plasma LDL-C compliance (< 1.4 mmol/L and a reduction of >50% from baseline) at 1, 3, and 6 months after PPCI; infarct size and EF measured by CMR at 6 months after PPCI; the occurrence of MACE.

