### Sample size calculation

Referring to our prior small sample size study, the MSI was higher in the PCSK9 inhibitor group (mean: 0.50; standard deviation [SD]: 0.16) than in the control group (mean: 0.41; SD: 0.15). To guarantee 90% power of the study at a significance level of 0.05, at least 64 patients per group will be needed. Considering a dropout rate of 20%, the required sample size is 160 (80 patients in each group). PASS 15 was used to calculate the sample size.

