### Statistical analysis

Continuous variables (including the primary endpoint) will be expressed as mean (SD) or median (interquartile rage) and will be compared using the *t*-test or the Mann-Whitney *U* test, as appropriate. Categorical variables will be expressed as counts and percentages and compared using the χ2 test or Fisher's exact test, as appropriate. We plan to assess the consistency of the treatment effect on the primary endpoint among three pre-specified subgroups that will be analyzed individually and then in a multivariate model. The following subgroup analyses are planned: age: < 60 years vs. ≥60 years; sex: female vs. male; duration from symptom onset to study drug infusion: < 3 h vs. 3–24 h. Safety analyses will include tabulation of the type and frequency of all adverse events and severe adverse events. All primary and secondary endpoints will be analyzed on an intention-to-treat basis (all patients will be analyzed as part of their designated treatment group) and protocol-based premise (analyses will only be performed as part of their designated treatment group when the patient received their designated treatment). For the intention-to-treat analysis, all patients who have provided written informed consent and who have been randomized in the study will be included in the analysis sample, regardless of whether they have received the correct treatment or whether there is crossover. For the protocol-based analysis, only registered patients who received the specified treatment will be included in the analysis sample. Patients who are lost to follow-up will be eliminated at the time of the last known contact. *P* values and confidence intervals will be two-sided with a significance level of 0.05.

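### Centre is in neither the randomisation strata nor the stated MSI comparison; the planned test is valid but gives up some precision that a centre term would recover

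*Protocol article*

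**What the plan says.** Under Study design, the article names the sites: "The centers of this study include Tongren Hospital, Chest Hospital, Tenth People's Hospital, and Ninth People's Hospital in Shanghai". Under Randomization, "Eligible patients will be randomized 1:1 to the PCSK9 inhibitor group or the control group" through a web response system, "stratified by age (≤ 60/>60; 2 categories), gender (female/male; 2 categories), time from symptom onset (< 3/3–24 h; 2 categories". That is 2 × 2 × 2 = 8 cells, and hospital is not one of the factors.

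Under Study endpoints, "The primary endpoint is MSI measured by CMR at 1 week after the index PPCI". Under Statistical analysis, continuous variables, expressly including this endpoint, "will be compared using the *t*-test or the Mann-Whitney *U* test, as appropriate". The only model mentioned is for consistency of effect, across "three pre-specified subgroups that will be analyzed individually and then in a multivariate model". Those subgroups are age, sex and time from onset, so centre does not enter there either.

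The sample size rests on the 20-patient pilot: "the MSI was higher in the PCSK9 inhibitor group (mean: 0.50; standard deviation [SD]: 0.16") "than in the control group (mean: 0.41; SD: 0.15"). It makes no allowance for variation between hospitals, although the Discussion says that the number of centres was expanded from the pilot.

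**The concern.** MSI is a cardiac magnetic resonance (CMR) measurement taken after an operator-dependent procedure, so its average level may differ between hospitals. Where it does, two things follow from a pooled two-sample test.

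- The between-hospital spread counts as residual noise and widens the confidence interval.
- The arms can differ by chance in how many patients each hospital contributes, because allocation is not balanced within hospital.

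Adjusting for age, sex and onset time would not remove this variation. At stake is some of the 90% power that the trial was sized for. The same applies to the 6-month infarct size and ejection fraction (EF).

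**Working it through.** **Inputs from the article.** Means 0.50 and 0.41, so the difference is 0.09. SDs 0.16 and 0.15. Two-sided 5% level, 90% power, 64 per arm analysed, 20% dropout, four hospitals.

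**Assumed input.** r is the share of MSI variance that lies between centres. The article gives no value, so 5%, 10% and 15% are shown, with 2% and 20% as outer points.

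**Step 1: the plan's own figure.**
- Pooled SD = √((0.16² + 0.15²)/2) = 0.1551.
- Standard error at 64 per arm = 0.1551 × √(2/64) = 0.0274.
- Noncentrality = 0.09/0.0274 = 3.28 on 126 degrees of freedom, which gives 90.3% power. With 63 per arm it is 89.8%, so 64 is the smallest number that reaches 90%.
- 64/0.80 = 80 per arm, 160 in total.

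The stated sample size reproduces and is not in question.

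**Step 2: the planning SD already contains centre variation.** Adjustment leaves a residual SD of 0.1551 × √(1 − r).

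| r | Residual SD | Fall in SE | Power, unadjusted | Power, adjusted |
|---|---|---|---|---|
| 2% | 0.1535 | 1% | 90.3% | 90.8% |
| 5% | 0.1512 | 2.5% | 90.3% | 91.7% |
| 10% | 0.1471 | 5% | 90.3% | 93.0% |
| 15% | 0.1430 | 8% | 90.3% | 94.2% |
| 20% | 0.1387 | 11% | 90.3% | 95.4% |

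**Step 3: centre variation comes on top of the pilot SD.** The total SD becomes 0.1551/√(1 − r), and the planned test bears all of it. Adjustment would bring power back to about 90.3%.

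| r | Total SD | Power, unadjusted, 64 per arm | Per arm for 90% |
|---|---|---|---|
| 2% | 0.1567 | 89.7% | 65 |
| 5% | 0.1591 | 88.8% | 67 |
| 10% | 0.1635 | 87.1% | 71 |
| 15% | 0.1682 | 85.2% | 75 |
| 20% | 0.1734 | 83.0% | 79 |

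**Step 4: validity of the planned test, by simulation.** There were 8,000 runs per setting: 128 patients, 64 per arm, allocated without regard to centre, with four centres of equal size or in shares of 50/20/20/10%.
- The unadjusted estimate averaged 0.090 under a true difference of 0.09.
- Type I error of the t-test was 4.7% to 5.3%.
- At r = 10%, power was about 90% unadjusted and about 93% adjusted. At r = 20% it was about 90% and 95%.
- At r = 0, adjusting cost under 1 point (for example 90.3% against 89.6% with equal centres).

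**Step 5: chance imbalance.** With four equal centres of 32, a given centre splits 20:12 or worse with probability 0.15, and at least one of the four does so with probability about 43%. With centres of 70, 30, 18 and 10, the chance that at least one is split 60:40 or worse is about 90% (about 67% for strictly worse). Small centres drive that figure and carry little weight in the estimate, so it says little about harm.

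**The case against.** The strongest objection is that the planned analysis is valid. Allocation is randomised 1:1, so hospital mix is independent of arm in expectation. This stands. A reader might infer from Step 5 that the trial cannot tell a drug effect from a difference in site mix. The documents do not support that: the simulation shows no bias and a correct error rate. Where the SD includes centre variation, site-mix error is part of the ordinary standard error of 0.0274. It is already inside the confidence interval and must not be added to it.

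The size is also assumed throughout. No figure for between-centre variation is given, all four hospitals are in one city, and care follows published guidelines. At r = 2% the gain in Step 2 is half a point. This stands too, and it limits the severity.

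Two further inferences are tempting and should not be drawn. The article does not say who reads the scans, so site differences in reading cannot be asserted; central reading would remove that component but not differences in operators or scanners. Table 2 shows no window around the 1-week visit, but that is not evidence that scan day differs by hospital.

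Last, covariates are often left to an analysis plan, and one may exist unseen. That would answer the point if the article were silent on the primary test. It names one, without covariates, so a plan that added centre would be changing a stated method.

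**Conclusion.** The point holds as a matter of efficiency. Centre is absent from both the strata and the stated MSI comparison, and a better method is available for the same data. The planned test remains unbiased with correct type I error.

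For assumed centre shares of 5% to 15%, the choice is worth 1.4 to 3.9 points of power if the planning SD includes centre variation (91.7 − 90.3 and 94.2 − 90.3). It is worth 1.5 to 5.1 points if that variation comes on top of the pilot SD (90.3 − 88.8 and 90.3 − 85.2). In the second case the unadjusted test falls below its 90% target. The documents do not show which case applies or what the true share is. These figures refer to the t-test, with the pilot difference and SDs taken as true. Severity is low.

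**What to change.** Replace the unadjusted primary comparison with a linear model of MSI on treatment, with centre as a four-level factor together with the three stratification factors. Use the same model for 6-month infarct size and EF. Show the MSI effect by centre descriptively, without a test. State this before any comparison of outcomes by arm.

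The randomisation need not change. Adding centre as a full stratum would make 8 × 4 = 32 cells for 160 patients, about 5 per cell, so adjustment in the analysis is the practical route.

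The centre term uses 3 of about 126 degrees of freedom, needs no new data, and loses under 1 point of power if hospitals do not differ. The text change is a sentence or two under Statistical analysis.

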### Interventions and follow-up

After grouping, enrolled patients will undergo PPCI with new-generation drug-eluting stents. Immediately after PPCI, patients grouped in the PCSK9 inhibitor group will be injected with alirocumab subcutaneously at a dose of 75 mg after the PPCI, followed by injections at the same dose every 2 weeks for 3 months on the basis of conventional treatment. Patients in the control group will receive conventional treatment in accordance with the published guidelines, including dual anti-platelet therapy and statins (15). Patients will be evaluated at 1 week and at 1, 3, and 6 months after the index PPCI, and the occurrence of clinical events will be monitored. As the primary endpoint, the MSI will be measured by CMR at 1 week after PPCI. As the key secondary endpoints, the infarct size and ejection fraction (EF) will also be measured by CMR at 6 months after PPCI. Additionally, the peak time of creatine kinase (CK)-MB and troponin I (TnI)/TnT, as well as the postoperative fall time of the ST segment on electrocardiography (ECG) will be recorded. Plasma LDL-C compliance rate (< 1.4 mmol/L and reduction >50% of baseline) and the occurrence of major adverse cardiovascular event (MACE: a composite of cardiovascular death, non-fatal myocardial infarction, stent thrombosis, repeat revascularization, stroke, and heart failure needed to be hospitalized) will be recorded at 1, 3, and 6 months after PPCI (16). Besides, medications at discharge will be recorded, especially those that affect cardiac remodeling. The investigators will follow up with the patients by office visits or telephone contact. The data collected during all follow-ups will be submitted to the original documents. If any patient is admitted to a non-research hospital again, every effort will be made to obtain the original data from the hospital. For all re-infarctions, ECG and myocardial enzyme data will be obtained and recorded. The following events will lead to termination of the patient's follow-up: (1) death; (2) voluntary withdrawal; (3) evacuation of patients by the investigators based on clinical manifestations; and (4) loss to follow-up (informal withdrawal). The follow-up schedule is shown in Figure 1 and Table 2.

**Table 2 T2:** Timetable of activities planned during the study.

**Time point**	**Before operation**	**Follow-up**			
		**1 week**	**1 month (±10 days)**	**3 months (±20 days)**	**6 months (±20 days)**
Informed consent	×				
Demographics/medical history	×				
Randomization	×				
Coronary angiography	×				
Fasting blood glucose	×				
Blood routine test	×	×			
Creatinine, urea nitrogen	×	×			
Electrocardiography	×	×			
CK, CK-MB, TnI/TnT	×	×			
Echocardiography	×	×			×
TC, LDL-C, TG	×	×	×	×	×
CMR		×			×
Medication		×	×	×	×
Drug side effects		×	×	×	×
MACE		×	×	×	×

CK, creatine kinase; CK-MB, creatine kinase isoenzymes; TnI/TnT, troponin I/troponin T; TC, total cholesterol; LDL-C, low-density lipoprotein cholesterol; TG, triglyceride; CMR, cardiac magnetic resonance imaging; MACE, major adverse cardiovascular event.

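### Investigator removal on clinical grounds ends outcome follow-up, not only study treatment, which conflicts with the promised intention-to-treat analysis of the endpoints after 1 week

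*Protocol article*

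**What the plan says.** In the Protocol article, the section Interventions and follow-up introduces a list with "The following events will lead to termination of the patient's follow-up". The list has four items: death, voluntary withdrawal, removal by the investigator, and loss to follow-up. The third reads "3) evacuation of patients by the investigators based on clinical manifestations". The article does not say which clinical states qualify, and it nowhere provides for outcome data to be collected after such a removal.

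The same section schedules MACE and LDL-C at 1, 3 and 6 months and states that "the infarct size and ejection fraction (EF) will also be measured by CMR at 6 months after PPCI". Study design describes a "multicenter, prospective, open-label, randomized controlled clinical trial".

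The Statistical analysis section says "All primary and secondary endpoints will be analyzed on an intention-to-treat basis". It defines that population so that "all patients who have provided written informed consent and who have been randomized in the study will be included in the analysis sample", and adds "regardless of whether they have received the correct treatment or whether there is crossover". It also says "Patients who are lost to follow-up will be eliminated at the time of the last known contact".

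**The concern.** Stopping study treatment and stopping follow-up are different things, and an intention-to-treat analysis depends on keeping them apart. Here the investigator's decision ends follow-up itself. The person deciding knows the allocation, and the stated ground is the patient's clinical condition, which may lie close to the outcomes being counted (heart failure admission, re-infarction, EF). Some of the patients removed could therefore be those whose later outcomes matter most, and the removals need not be balanced.

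Death and true loss are largely unavoidable. This item creates missing data by rule. At stake are the credibility of MACE and of 6-month infarct size and EF, which the article calls key secondary endpoints, and the completeness of later LDL-C and adverse-event data.

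**Working it through.** **1. The two sections side by side.** Interventions and follow-up ends follow-up at investigator removal. Statistical analysis requires every randomized patient in the analysis of every endpoint. A patient removed at, say, month 2 belongs to the intention-to-treat sample but will have no 6-month CMR and no MACE record after month 2. The sample can be defined as promised, but the data to fill it are not collected.

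**2. Does another sentence restore the data?** No.
- The commitment to obtain original records concerns readmission to a non-research hospital. It does not reopen follow-up that has been ended.
- The sentence on elimination at last contact names patients lost to follow-up, which is a separate item in the list of four. How it applies to removed patients is unclear.
- The separate protocol-based analysis already deals with patients who did not receive their treatment, so it does not require their follow-up to end.

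**3. Which endpoints are exposed, by timing.**
- MSI at 1 week: only if removal falls between randomization (before PPCI) and the 1-week CMR.
- MACE and LDL-C at 1, 3 and 6 months: everything after removal. Events recorded before removal are kept.
- Infarct size and EF at 6 months: any removal before the 6-month CMR.

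**4. The plan's own figure.** The sample size uses MSI 0.50 (SD 0.16) versus 0.41 (SD 0.15), two-sided 0.05, 90% power.
- Common SD = √((0.16² + 0.15²)/2) = 0.155; difference = 0.09.
- The normal approximation gives 63 per group. The noncentral t gives power 89.8% at 63 and 90.3% at 64, so 64 reproduces.
- 64/0.80 = 80 per group, 160 in total.

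The allowance is 80 − 64 = 16 patients per arm. It protects power for MSI. It gives no protection against bias from selective removal.

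**5. Illustration for a 6-month continuous outcome.** All inputs except 80 per arm are assumptions: no true effect; outcome standardized to SD 1; a fraction f removed from one arm only, being the worst on a clinical marker with correlation ρ to the outcome; nobody removed from the other arm.
- Bias (SD units) = ρ·φ(z_f)/(1 − f), where φ is the standard normal density and z_f its f-quantile.
- SE = √(1/(80(1 − f)) + 1/80), with the SD held at 1 as an approximation.
- Type I error = Φ(bias/SE − 1.96) + Φ(−bias/SE − 1.96).

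| Removed from one arm | ρ | Bias (SD) | Type I error |
|---|---|---|---|
| 4 of 80 (5%) | 0.3 | 0.033 | 5.5% |
| 4 of 80 | 0.5 | 0.054 | 6.3% |
| 4 of 80 | 1.0 | 0.109 | 10.4% |
| 8 of 80 (10%) | 0.3 | 0.058 | 6.5% |
| 8 of 80 | 0.5 | 0.097 | 9.2% |
| 8 of 80 | 1.0 | 0.195 | 22.5% |

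Worked case: f = 0.05, ρ = 1. Bias = 0.1031/0.95 = 0.109; SE = √(1/76 + 1/80) = 0.160; ratio 0.68; type I error about 0.104.

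Both removal counts lie inside the 16 per arm allowed for dropout. If both arms lost the same fraction by the same criterion, the two shifts would cancel under this model. The table therefore shows what one-sided removal could do, not what will happen.

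**The case against.** **The primary endpoint is largely untouched.** The sample size rests on MSI at 1 week, and only removal in the first days reaches it. A reader might infer that the whole intention-to-treat analysis is undermined. The timing does not support that, and this limits the severity.

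**Cause and imbalance are inferred.** The article does not say what prompts removal, and the rule applies to both arms. A reader might argue that only the alirocumab arm has a study drug to come off. But stopping the drug is not among the four terminating events, so this does not establish an asymmetry. Where the clinical event is itself a re-infarction or a heart-failure admission, it is a MACE component to be recorded when it occurs, and later removal does not erase it.

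**Dramatic MACE examples are constructed.** Suppose 12/80 true events per arm, with 5 alirocumab patients and 1 control patient removed before their events. The trial would record 7/80 (8.8%) versus 11/80 (13.8%), or 7/75 (9.3%) versus 11/79 (13.9%) if removed patients leave the denominator. A reader might take this as a demonstrated false benefit. Every count is invented, and all six removed patients must go on to an event. Even then the first comparison has SE √(0.1125 × 0.8875 × 2/80) = 0.050, z about 1.0 and p about 0.32.

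**The loss is not beyond analysis.** Baseline, 1-week and all other data before removal remain, and missing-data methods may sit in an analysis plan that is not shown. To say that the damage cannot be repaired would be too strong. What stands is that any such method would rest on assumptions that the collected data cannot test, for data the trial could have collected.

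**Conclusion.** The point holds in a limited form. The article states a rule that ends outcome follow-up on an undefined clinical judgement in an open-label trial, and this conflicts with its own intention-to-treat commitment. The conflict rests on the text alone. That removals will relate to outcome or differ by arm is a reasonable inference, not something the document shows.

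The actual bias cannot be computed because no removal rate is given. The illustrative type I error of 5.5% to 22.5% depends on one-sided removal of 4 to 8 patients and on ρ between 0.3 and 1.0. The exposure falls mainly on MACE, 6-month infarct size and EF, and later LDL-C and adverse events. Severity: should-fix.

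**What to change.** In Interventions and follow-up:
- Delete item (3) as a reason to end follow-up.
- State that a patient removed from study treatment stays in outcome follow-up to 6 months: MACE by visit or telephone (telephone contact is already allowed), and the scheduled CMR where it is feasible and the patient still consents.
- Let only death, withdrawal of consent to follow-up, or true loss end follow-up. Item (2) should accordingly refer to consent to follow-up.

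In Statistical analysis, reconcile the sentence on elimination at last contact with this rule and with the intention-to-treat definition, so that it covers true loss only and says what elimination means.

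The cost is protocol wording with ethics committee approval, a reminder to sites, and a few more calls or visits within the existing schedule. The change should be made promptly, because assessments missed in the meantime, above all the 6-month CMR, cannot be made up later. Nothing here concerns when study treatment should stop.
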